## Abstract

**Background:**

Insomnia affects almost one in four military service members and veterans. The first-line recommended treatment for insomnia is cognitive-behavioral therapy for insomnia (CBTI). CBTI is typically delivered in-person or online over one-to-four sessions (brief versions) or five-to-eight sessions (standard versions) by a licensed doctoral or masters-level clinician with extensive training in behavioral sleep medicine. Despite its effectiveness, CBTI has limited scalability. Three main factors inhibit access to and delivery of CBTI including restricted availability of clinical expertise; rigid, resource-intensive treatment formats; and limited capacities for just-in-time monitoring and treatment personalization. Digital technologies offer a unique opportunity to overcome these challenges by providing scalable, personalized, resource-sensitive, adaptive, and cost-effective approaches for evidence-based insomnia treatment.

**Methods:**

This is a hybrid type 3 implementation-effectiveness randomized trial using a scalable evidence-based digital health software platform, NOCTEM™’s Clinician-Operated Assistive Sleep Technology (COAST™). COAST includes a clinician portal and a patient app, and it utilizes algorithms that facilitate detection of sleep disordered patterns, support clinical decision-making, and personalize sleep interventions. The first aim is to compare three clinician- and system-centered implementation strategies on the reach, adoption, and sustainability of the COAST digital platform by offering (1) COAST only, (2) COAST plus external facilitation (EF: assistance and consultation to providers by NOCTEM’s sleep experts), or (3) COAST plus EF and internal facilitation (EF/IF: assistance/consultation to providers by NOCTEM’s sleep experts and local champions). The second aim is to quantify improvements in insomnia among patients who receive behavioral sleep care via the COAST platform. We hypothesize that reach, adoption, and sustainability and the magnitude of improvements in insomnia will be superior in the EF and EF/IF groups relative to the COAST-only group.

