## Outcome measures

Table 2 summarizes the schedule of enrollment, interventions, and assessments for participating providers. Clinician-centered, implementation outcomes from the reach, effectiveness, adoption, implementation, and maintenance (RE-AIM) framework [67], see also re-aim.gov, include reach, adoption, and maintenance (sustainability). Provider reach is defined as the ratio of providers who provide informed consent to participate and complete the COAST training over the number of providers who received information about the trainings via emails, personal invitations, and other communication means targeting behavioral health providers. Patient reach is defined as the ratio of patients who consent to use the app relative to the number of patients deemed eligible to use the app. Adoption is defined as the ratio of newly trained providers who initiate the use of the COAST platform with patients (i.e., provide a patient with an app code) over the total number of providers who completed the COAST training (i.e., trained users + trained non-users). Sustainability is determined by comparing the frequency of COAST platform use by the trained providers across the three groups at the 3-, 6-, and 12-month assessments to measure potential changes on these domains over time.

**Table 2 Tab2:** Providers’ schedule of enrollment, interventions, and assessments for this hybrid type 3 implementation-effectiveness randomized trial

			Study period				
	Enrollment	Consent	Baseline	Post-randomization			
**Timepoint**	***-t***_***1***_	**0**	***t1***	***Familiarization***	***3 months***	***6 months***	***12 months***
**Enrollment:**	X						
Complete sleep training	X						
Informed consent		X					
NOCTEM COAST training			X				
Randomization			X				

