**Assessments:**							
Demographics and practice survey			X				
Post-training survey			X				
Organization readiness for implementing changes			X			X	X
System usability scale			X	X		X	X

Fidelity is evaluated by quantifying the adherence (or discrepancy) between algorithm-recommended interventions relative to interventions that are sent to patients by providers. As in some cases there may be valid clinical reasons why a provider determines a patient should not receive the algorithm-recommended intervention (e.g., sickness, incompatible with assigned duties), we expect a rate of non-adherence of approximately 20%—noting we will not be accessing patients medical records to validate the potential reasons for deviations.

The primary patient-centered outcome measure of treatment effectiveness is the Insomnia Severity Index (ISI [32]). Other symptom domains to be assessed are summarized in Table 3, and include the PTSD Checklist-5 (PCL-5 [47, 48]), the 8-item Patient Health Questionnaire (PHQ-8 [49]) to assess symptoms of depression, the 7-item Generalized Anxiety Disorder scale of the PHQ (GAD-7 [50]), the PEG, a 3-item validated and reliable pain measure [68], and the 4-item PROMIS Satisfaction with Social Roles and Activities [69]. For patients, the total time required to complete the battery is approximately 20 min. The battery will be completed through the NOCTEM app at baseline, post-treatment, and again 3 and 12 months post-treatment.

**Table 3 Tab3:** Self-report measures of sleep and daytime symptoms to be completed by participating patients at baseline, post-intervention, and at the follow-up assessments

Domain	Scale	Number of items	Time to complete

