The first hypothesis is that providers randomized to one of the two COAST+ conditions will show greater reach, adoption, and sustainability at the 3- and 12-month follow-ups compared to providers randomized to the COAST only. For adoption, we will use a test for two proportions to determine whether reach and adoption differ between COAST versus COAST+EF and COAST+EF/IF at the 3- and 12-month follow-ups. With at least 8 providers in COAST and 16 in COAST+EF and COAST+EF/IF, as well as a reach and adoption between 0.50 and 0.60 in COAST, we will have 0.80 power (alpha = 0.05) to detect a difference in proportions between COAST and COAST+ of 0.39–0.46. For sustainability, each provider’s average number of interactions per patient over time and number of newly enrolled patients each month for each of the 12 months will be computed. We will then fit a generalized linear mixed effects model to regress number of interactions on group (COAST versus COAST+) and time. The group-by-time interaction will also be tested. Models will include a random intercept and time effect. With six repeated measures (autocorrelation 0.60–0.80) and 24 providers (8 COAST and 16 COAST+EF and COAST+EF/IF), we expect 0.80 power (alpha = 0.05) to detect differences of 0.99–1.11 between groups. With 12 repeated measures, we expect power to detect differences of 0.97–01.10 between groups.

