The second hypothesis is that COAST+EF and COAST+EF/IF will yield greater improvements in patient insomnia symptom severity than COAST only over the acute 6-week intervention period. We will compute the change in ISI from baseline to 6 weeks (∆ISI = baseline ISI − 6-week ISI), with higher ∆ISI values indicating a greater improvement over time. We will use a mixed effects model to regress ∆ISI on group, accounting for nesting within providers through a random effect and including relevant covariates. We will extract estimates from the model to compute the standardized mean difference *d* [70, 71] and 95% confidence interval between COAST and COAST+ (EF; EF/IF) accounting for patients nested within providers. Second, using a mixed effects model with a random clinician effect, we will regress ISI at baseline and 6 weeks of treatment (COAST versus COAST+EF and COAST+EF/IF), time, and their interaction, controlling for relevant covariates. A significant treatment-by-time effect will indicate that the change in ISI differs between COAST and COAST+EF and COAST+EF/IF. Assuming an average of 12 providers per group (8 in COAST and 16 in COAST+EF and COAST+EF/IF) and 36 patients per clinician, we expect 0.80 power (alpha = 0.05) to detect a standardized mean difference of 0.232 between groups. We will also evaluate the extent to which COAST+EF is not inferior to COAST+EF/IF as measured by changes on the ISI over the acute 6-week intervention period. This non-inferiority hypothesis will be tested with the general form—H_0_: COAST+EF is inferior to COAST+EF/IF versus H_1_: COAST+EF is non-inferior to COAST+EF/IF. Using the methods described above, we will compute the standardized mean difference *d* and 95% confidence interval [*d* (95% CI)] for COAST+EF − COAST+EF/IF of ∆ISI. As positive values of ∆ISI indicate more improvement, a positive *d* is in favor of COAST+EF and a negative *d* is in favor of COAST+EF/IF. We will use a non-inferiority margin (NIM) of − 0.50 and declare COAST+EF to be non-inferior to COAST+EF/IF if the lower bound of the 95% CI for *d* is > − 0.50. We will declare COAST+EF to be inferior to COAST+EF/IF if the lower bound of the 95% CI for *d* is ≤ − 0.50. For example, if *d* (95% CI) = − 0.10 (− 0.40, 0.20), we would declare COAST+EF as non-inferior to COAST+EF/IF because − 0.40 > − 0.50. However, if *d* (95%CI) = − 0.40 (− 0.70, − 0.10), we will declare COAST+EF to be inferior because − 0.70 ≤ − 0.50. These one-sided decision rules equate to requiring the effect size of the COAST+EF to COAST+EF/IF comparison to have no more than moderate strength (|d| = 0. 5), in favor of COAST+EF/IF. The NIM of |d| = 0.5 set to determine non-inferiority is stringent as it represents 50% of the effect size reported in recent meta-analyses [50, 72, 73]. Assuming 8 providers per group and 36 patients per clinician, an intra-class correlation of 0.01 [74], a non-inferiority margin of 0.50, and a true difference of δ = 0, we expect > 0.99 power to reject our null hypothesis and conclude that COAST+EF is non-inferior to COAST+IF/EF.

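### The Hypothesis 2 ISI comparison uses only patients of providers who took up COAST after learning their arm, so it is not fully randomized if facilitation raises adoption as Hypothesis 1 predicts

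*Protocol article*

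**What the plan says.** The second aim in the Abstract is to "quantify improvements in insomnia among patients who receive behavioral sleep care via the COAST platform".

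Providers are the randomized units and are told their arm before they enroll patients (Randomization of providers). The treating provider has the final say on each patient's inclusion (Selection criteria and enrollment).

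On uptake, Outcome measures states: "Adoption is defined as the ratio of newly trained providers who initiate the use of the COAST platform with patients". Starting use means giving a patient an app code, and trained providers who never do so stay in the denominator. The plan therefore allows for non-adopters.

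On the ISI, the same section states: "The battery will be completed through the NOCTEM app at baseline, post-treatment, and again 3 and 12 months post-treatment". No other route for collecting it is described.

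Hypothesis 1 (Objective, aims, and hypotheses) predicts greater reach, adoption and sustainability in the two facilitated arms, without giving a size. Its power statement assumes "as well as a reach and adoption between 0.50 and 0.60 in COAST" and claims 0.80 power "to detect a difference in proportions between COAST and COAST+ of 0.39–0.46".

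Hypothesis 2 (Statistical analyses plan and power calculations) is that "COAST+EF and COAST+EF/IF will yield greater improvements in patient insomnia symptom severity than COAST only over the acute 6-week intervention period". It is tested by regressing change in ISI on group with a random provider effect. A second mixed model tests a treatment-by-time effect. The same section tests non-inferiority of COAST+EF to COAST+EF/IF with a margin of 0.50 SD.

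**The concern.** A provider who never issues an app code contributes no ISI data. The Hypothesis 2 models therefore run on patients of adopters only, and adoption is an event after randomization that Hypothesis 1 says the arm changes. The better Hypothesis 1 is borne out, the less Hypothesis 2 compares like with like.

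Suppose providers who take up COAST unaided also tend to get better results. The COAST-only mean is then inflated relative to COAST+, and a real benefit of facilitation can be hidden. If the relation runs the other way, an apparent benefit can be produced. This would remain even if every adopter enrolled 36 unselected patients. It is separate from the power lost through non-adoption and from any choice of patients by providers who know their arm.

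**Working it through.** **Inputs from the article (Statistical analyses plan and power calculations).** COAST-only adoption 0.50 to 0.60; detectable difference 0.39 to 0.46; 8 v 16 providers; 36 patients per provider; target standardized mean difference 0.232 at 0.80 power; intraclass correlation (ICC) 0.01. The ICC is stated for the non-inferiority calculation. Carrying it over to the superiority test is an assumption. Alpha is 0.05, taken as two-sided.

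**Reproducing the plan's figures.**
- Adoption: exact enumeration of the two-sided pooled z test with 8 v 16 providers gives power 0.800 for 0.50 v 0.96 and 0.801 for 0.60 v 0.987 (difference 0.387, which rounds to 0.39). The range 0.39–0.46 reproduces.
- ISI: design effect 1 + 35 × 0.01 = 1.35; SE = √[1.35 × (1/288 + 1/576)] = 0.0839. Power at 0.232 is Φ(0.232/0.0839 − 1.96) = 0.79 for 8 v 16 providers. With 12 v 12 providers and a noncentral t on 22 df it is 0.80. The figure reproduces with every randomized provider contributing 36 patients.

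**Who would supply ISI data at the detectable difference.**
- 0.50 v 0.96: 8 × 0.50 = 4.0 COAST-only and 16 × 0.96 = 15.4 COAST+ providers.
- 0.60 v 0.99: 8 × 0.60 = 4.8 and 16 × 0.99 = 15.8.

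**Illustrative selection bias.** Assume adopters are the top share p on a normal provider trait, the same trait in both arms. Let it have correlation ρ with the provider's mean change in ISI, whose SD is √ICC in units of the total SD. The mean trait among adopters is φ(z)/p, where z is the normal cut-off that leaves a share p above it.
- p = 0.50 gives 0.798 and p = 0.96 gives 0.090, a difference of 0.708.
- Bias = ρ × √0.01 × 0.708.

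| ρ | Bias (SD), 0.50 v 0.96 | Share of 0.232 | Bias (SD), 0.60 v 0.99 |
|---|---|---|---|
| 0.3 | 0.021 | 9% | 0.019 |
| 0.5 | 0.035 | 15% | 0.031 |
| 1.0 | 0.071 | 31% | 0.062 |

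A positive ρ biases the contrast against COAST+, a negative ρ in its favor. The documents give no value or sign for ρ.

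**Non-inferiority.** Even if the whole 0.50 v 0.96 gap lay between COAST+EF and COAST+EF/IF, with ρ = 1, the bias would be 0.071 against a margin of 0.50.

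**Does anything in the article repair it?** The random provider effect handles clustering, not absent clusters. Multiple imputation covers individuals with missing values, not patients never enrolled. The named covariates are site, age, sex, rank and psychotropic medication; provider characteristics enter only exploratory analyses. Replacing providers who withdraw (Discussion) does not restore the randomized set. The minimum of 36 patients per provider sits uneasily with planned adoption of 0.50 to 0.60 and does not prevent non-adoption.

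**The case against.** Several objections stand.
- The 0.39–0.46 is what 24 providers can detect, not what the trial expects. A reader might infer that the plan forecasts 0.96 to 0.99 adoption under facilitation. It does not, and a smaller gap means a smaller bias.
- At the plan's own ICC the bias is small, and 31% of the target requires adoption to be determined entirely by provider effect. An ICC of 0.05 would raise the share to 34% (ρ = 0.5) or 68% (ρ = 1), but no such ICC appears in the documents.
- The Abstract's second aim is descriptive, states its population correctly and contains no error. The difficulty lies in the between-arm models.
- Adoption is an outcome in its own right, with non-users counted. A strategy under which many providers treat nobody would show as failing there.
- Provider background is collected at the outset and explored against outcomes, so differences between adopters can be examined.

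None of this makes the ISI contrast a comparison of the groups as randomized. Finer estimand wording may be left to the analysis plan, but the article itself fixes the hypothesis, the data source and the model, and states the hypothesis as superiority of the facilitated arms.

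**Conclusion.** The point holds as a limit on interpretation. If adoption differs between arms, the Hypothesis 2 contrast describes patients of adopting providers and cannot by itself be credited to facilitation. For illustration, at 0.50 v 0.96 adoption and ICC 0.01, the provider-level bias is about 0.02 to 0.07 SD for ρ from 0.3 to 1, sign unknown. That rests on the normal selection model and on using the same ICC for the superiority test. If adoption turns out similar across arms, this particular problem largely disappears.

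A reader might go further and conclude that randomization is lost altogether or that the ISI comparison is worthless. The documents do not support that: the size is modest at the plan's own ICC. Nor is the non-inferiority test seriously threatened, since the bias is negligible against a margin of 0.50 at that ICC and nothing in the article suggests that adoption differs between COAST+EF and COAST+EF/IF.

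**What to change.** Keep the change-in-ISI models and amend the Hypothesis 2 text in Statistical analyses plan and power calculations as follows.

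1. Define the target as the difference in change in ISI among patients of adopting providers.
2. State that it will not be read as a causal effect of facilitation if adoption differs between arms.
3. Report it beside adoption by arm, with a sensitivity analysis adjusting for the provider characteristics already collected at enrollment (experience, background, familiarity with behavioral sleep medicine, use of digital tools).
4. Add a supportive provider-level analysis that includes every randomized provider. One example is the number of patients with ISI < 8 at 6 weeks (the remission cut-off cited in the Background) per randomized provider, with zero for non-adopters. The zero means no remission recorded through COAST, not that those providers' patients did badly.

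The cost is a slightly weaker claim for Hypothesis 2 and a little more analysis of data already collected. The supportive count mixes patient volume with benefit and partly repeats the adoption result, so it should not replace the ISI outcome.

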**Discussion:**

Digital health technologies and machine learning-assisted clinical decision support tools have substantial potential for scaling access to insomnia treatment. This can augment the scalability and cost-effectiveness of CBTI without compromising patient outcomes. Engaging providers, stakeholders, patients, and decision-makers is key in identifying strategies to support the deployment of digital health technologies that can promote quality care and result in clinically meaningful sleep improvements, positive systemic change, and enhanced readiness and health among service members.

**Trial registration:**

ClinicalTrials.gov NCT04366284. Registered on 28 April 2020.

## Background

This implementation-effectiveness hybrid type 3 trial [1, 2] aims to implement a large-scale, cluster-randomized pragmatic demonstration to inform behavioral sleep medicine practices and policies for active duty service members (ADSMs), veterans, and other beneficiaries with chronic insomnia disorder who receive care in military treatment facilities (MTFs) and affiliated clinics and wellness centers. Chronic insomnia disorder is defined as difficulty falling or staying asleep that persists for at least 3 months and is associated with daytime impairments [3]. These impairments span a variety of domains of functioning including memory and concentration difficulties, irritability, somatic symptoms, worry, and absenteeism. Insomnia is endemic among military personnel as well as veterans. Depending on the measurement method (e.g., self-report, sleep diary, diagnostic interview), insomnia affects between 24 and 90% of ADSMs and veterans who have deployed since 2001 [4–7]. Insomnia is also prevalent among non-deployed ADSMs [8–10].

Insomnia not only degrades military readiness, but also hinders resilience, quality of life, mood, and overall health [4]. In fact, insomnia is a robust risk factor for poor psychological and physical health outcomes [4–10], and is often comorbid with psychiatric and medical conditions such as posttraumatic stress disorder (PTSD), depression, suicidality, anxiety, alcohol use disorder, hypertension, chronic pain, obesity, and diabetes [5–14]. In the military population, insomnia symptoms have been associated with decreased resilience [15]. In a large study which evaluated 55,201 military personnel, those with insomnia symptoms reported lower self-rated health, were less likely to deploy, had increased days of missed work and healthcare utilization, and were more likely to be discharged early from the military [15].

The first-line recommended treatment for insomnia is cognitive-behavioral therapy for insomnia (CBTI) [16–19]. CBTI is typically delivered in-person (including via tele-health) over one-to-four sessions for brief versions, or five-to-eight sessions for the standard version, by a licensed doctoral or masters-level clinician with extensive training in behavioral sleep medicine [20–25]. Both brief and standard CBTI approaches yield comparable clinically meaningful improvements in insomnia severity [21, 26–30], with effect sizes in the moderate-to-very large range (Cohen’s *d* coefficients between .50 and 2.15). Response rates are also remarkable. For example, the Veterans Health Administration (VHA) national rollout of CBTI [14, 31] reported that, at post-treatment, 73% of 431 treated veterans endorsed Insomnia Severity Index [32] scores below the cutoff for moderately severe insomnia (ISI <  15), and that 35% no longer met criteria for insomnia (ISI < 8). A previous clinical trial with veterans undergoing a 4-week CBTI protocol reported response rates over 75% and remission rates of more than 50% [22]. CBTI has been shown to be effective for chronic insomnia, including insomnia that is comorbid with PTSD, anxiety, depression, alcohol and substance use disorders, suicidality, and chronic pain in both civilian and military samples [21, 33, 34]. Importantly, improvements in insomnia are maintained over time [35].

Despite its effectiveness, the limited scalability of CBTI impedes access to and delivery of evidence-based behavioral sleep medicine (EB-BSM) and contributes to the continuance of hypnotics as a common insomnia treatment. In a comprehensive study of sedative hypnotic medications in the military health system, ADSMs were significantly more likely than non-ADSMs to be prescribed this class of medications [30]. Notably, the ADSMs were markedly younger at 33.5 years of age compared to 59.1 years in the non-ADSMs. Approximately 10% of 18,000 surveyed ADSMs reported using sleep aids daily or almost daily. Their abuse potential, side effects, and link to increased risk of injurious behaviors raise serious health and safety concerns for all ADSMs due to their high-risk occupations [36–39].

Three main factors inhibit access to and delivery of CBTI to meet the needs of ADSMs. First, there is restricted availability of clinical expertise. Specialty sleep care clinics and expert behavioral sleep medicine providers are not readily available in the civilian sector [40–42] and across military treatment facilities (MTFs) and clinics, or in the more than 150 countries where US Armed Forces are stationed. Despite efforts to increase the number of providers trained in CBTI, shortfalls related to provider and geographic availability remain (e.g., many providers are clustered near urban, academic medical centers). Second, CBTI delivery formats (in-person or via telemedicine) are resource intensive. Even when available, the in-person delivery format of CBTI often creates barriers to receiving or adhering to treatment visit schedules due to travel distance (to and from the clinics), conflict with work and family schedules, childcare availability, and incompatibility with the demanding operational tempo of ADSMs [43]. To mitigate some of these barriers, online programs have been developed [44]. Online programs are self-administered (or unguided), and delivered without interaction with a dedicated clinician [43, 45–48]. Although these approaches are efficacious, they still require non-negligible time commitments from patients for several weeks to several months [43, 47–49], and attrition can be higher compared to clinician-assisted CBTI programs [43, 46, 49–51]. Third, there are limited capacities for just-in-time monitoring and treatment personalization. The current CBTI delivery formats (in-person or online) rely on scheduled weekly or bi-weekly appointments along with completion of homework, with no or limited capabilities for real-time (or near real-time) monitoring of adherence, intervention, and patient-clinician engagement. The available CBTI formats limit providers’ ability to prospectively monitor adherence, side effects, and improvements over time so that just-in-time recommendations can be delivered, and non-adherence or exacerbation of symptoms can be detected and addressed in a timely manner, which can enhance treatment outcomes. Furthermore, real-time patient-clinician interactions can augment patient engagement and the personalization and precision of care by allowing providers to adapt the frequency and duration of clinical engagement to best match individual patients’ needs (i.e., more complex patients may have more frequent or longer sessions compared to less complex patients). To address these challenges and effectively meet the insomnia needs of ADSMs, veterans, and beneficiaries, for evidence-based behavioral sleep medicine (EB-BSM) practices, innovative, scalable, personalized, resource-sensitive, adaptive, and cost-effective approaches are urgently needed.

Digital health (dHealth) technologies are becoming an increasingly popular means to overcome barriers related to the scalability, accessibility, and personalized delivery of evidence-based (EB) interventions. Some of the key current challenges in behavioral sleep medicine and advantages of leveraging dHealth technologies to overcome these challenges and support the delivery of EB-BSM are summarized in Table 1. Envisioned outcomes are also summarized in Table 1.

**Table 1 Tab1:** Summary of challenges to dissemination of evidence-based behavioral sleep medicine and gap bridging solutions offered by digital technologies, and targeted outcomes

Current challenges	Solutions offered by dHealth technologies	Targeted outcomes
Access to evidence-based behavioral sleep care geographically limited to some urban/academic centers	Accessibility not limited by geographical locations	Leverage providers to serve more patients over broader catchment area
Limited number of trained behavioral sleep providers	Provide clinical decision-making support for non-sleep providers and consultation with experts in behavioral sleep medicine	Harness patient preference for treatment delivery format [40]
Delivery of care limited to in-person or synchronous telemedicine encounters	Delivery of synchronous and asynchronous care to match “just-in-time” patient needs and clinical resources	Increased accessibility for individuals with restricted mobility, and individuals with responsibilities that conflict with typical office hours (e.g., childcare, work schedule)
Cost-effectiveness	Independent of brick-and-mortar locations and related costs	Enhanced workflow and patient volume with minimal impact on workload
	Harness non-traditional workforce in behavioral health	
Fixed treatment protocols, appointment schedules, and communication means	Timely and secure just-in-time communication and exchange of information between provider and patient	Optimize personalization of assessment and intervention plan, prospective monitoring of adherence, side effects, progress, and outcomes

We first iteratively developed a prototype of the dHealth sleep platform with 5 providers and research clinicians and 17 military ADSM and veterans with chronic insomnia and comorbid psychiatric symptoms and conditions including PTSD, depression, and/or anxiety. Following this prototype, we evaluated the usability of the dHealth system by research clinicians and changes in sleep and daytime psychiatric symptoms in a sample of 27 ADSM and veterans. We compared these findings with results from previous trials where brief or traditional CBTI was delivered in person to a comparable sample of ADSM and veterans. This preliminary work strongly suggests that delivering EB behavioral insomnia treatments using dHealth technology is acceptable and feasible [52], associated with clinically meaningful improvement in insomnia severity (Cohen’s *d* effect sizes = 1.93), as well as improvements for the daytime PTSD symptoms (Cohen’s *d* effect sizes = 1.19), depression (Cohen’s *d* effect sizes = 1.13), and anxiety (Cohen’s *d* effect sizes = 0.74) [27]. Furthermore, these clinically significant improvements in insomnia and daytime function were the result of an average 15 min of clinical interaction, total, over 4 weeks between each participant and their research clinician. This contrasts sharply with the two-to-eight 30–45-min sessions typically required by in-person or tele-health CBTI (total time of 90 to 360 min). A potential reduction in clinical time required per patient of 88 to 96% suggests a substantial improvement in cost-effectiveness and scalability without compromising clinical outcomes.

A subsequent process improvement project in MTFs and affiliated clinics with 19 providers and over 100 patients support the acceptability and feasibility of deploying dHealth technologies such as NOCTEM’s Clinician-Operated Assistive Sleep Technology (COAST™) in real clinical settings (unpublished data) with behavioral health providers outside of sleep specialty care clinics. However, demonstration of effective deployment and implementation strategies as well as clinical outcomes associated with of COAST in military treatment facilities across the Department of Defense remains to be determined. This is the goal of this randomized hybrid type 3 implementation-effectiveness trial.

